## 8.2. Analysis Population

Subjects who complete the CC or SC procedure and do not meet any of the withdrawal criteria will be included into the analysis population for statistical analysis.

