### **7.3.3. Randomization**

Before colonoscopy initiation, eligible subjects will be randomized in a 1:1 ratio to receive CC or SC.

Randomization will be based on a computer-generated randomization list prepared centrally by the sponsor. Randomization will be stratified by gender, age, and colonoscopy indication (screening, diagnostic, or surveillance) of subjects.

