### **7.3.4. Blinding**

The subject and the pathologist who performs the histopathological review will be blinded to the received procedure, while the operator will not be blinded to the study arm assigned to the subject. The investigator at each site will be unblinded to the assigned study arm of the subject, but will be blinded to the assigned study arm of the specimens when conducting the histopathological review

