### **7.3.7. Withdrawal of Subjects**

Participation in the study is completely voluntary, thus subjects can withdraw at any time during or after the procedure. Written consent will be obtained from all subjects. Withdrawing from the procedure has no negative implication on their colonoscopy examination and subsequent clinical care. A subject may be withdrawn from the research at the discretion of the endoscopist or the investigator. Subjects who meet any of the following withdrawal criteria may be withdrawn from the study.

Withdrawal criteria:

- (1) Subject who withdraws consent.
- (2) Poor bowel preparation based on the four-grade modified Aronchick Bowel Preparation Scale.
- (3) There is a clinical suspicion for hereditary polyposis syndrome or new case of IBD based on the colonoscopy per the investigator's judgement.
- (4) The colonoscopy procedure cannot be completed, either due to intolerance, stenosis, obstruction, huge occupying lesions, or solid stool.
- (5) The colonoscopy procedure is terminated due to any procedure-related complications.
- (6) Subjects with difficult anatomy or post-surgical anatomy preventing completion of the procedure using a standard colonoscope.

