## **7.4. Endpoints**

### **7.4.1. Primary Endpoint**

The primary endpoint is the ADR of the CC as compared with that of the SC. The ADR is defined as the percentage of subjects undergoing a complete colonoscopy, who have at least one histologically confirmed adenoma detected and removed.

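### The single analysis population is completers only, so neither the non-inferiority nor the superiority test compares all subjects as randomised

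*Protocol*

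**What the plan says.** Section 7.3.3 places assignment ahead of the procedure: "Before colonoscopy initiation, eligible subjects will be randomized in a 1:1 ratio to receive CC or SC".

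Section 7.3.7 lists six withdrawal criteria: withdrawn consent; poor bowel preparation; suspicion of hereditary polyposis or new inflammatory bowel disease arising from the colonoscopy; a procedure that cannot be completed (reasons include stenosis, very large lesions and solid stool); termination for a complication; and difficult or post-surgical anatomy. Subjects who meet one are permitted, not required, to be withdrawn. The section also says: "A subject may be withdrawn from the research at the discretion of the endoscopist or the investigator".

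Section 8.2 then sets the population: "Subjects who complete the CC or SC procedure and do not meet any of the withdrawal criteria will be included into the analysis population". Section 8.3 tests non-inferiority and, if that is met, superiority by a one-sided Fisher exact test at 0.025, without naming another set. The endpoint in section 7.4.1 carries the same restriction: "The ADR is defined as the percentage of subjects undergoing a complete colonoscopy".

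On blinding, section 7.3.4 says that "the operator will not be blinded to the study arm assigned to the subject" and, for the site, "The investigator at each site will be unblinded to the assigned study arm of the subject". Subjects and pathologists are blinded.

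**The concern.** A superiority claim draws its protection from comparing the groups that randomisation formed. Here membership of the only analysis set is settled after assignment, partly on what is seen during the examination, by people who know the arm.

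Some criteria plausibly track the outcome. Suspected polyposis and very large lesions point to lesion-rich subjects; poor preparation and solid stool limit what can be found. The polyposis criterion depends on what is seen, which the device is designed to change. Blinding of the pathologist does not protect this step, because an excluded subject never reaches the comparison.

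If exclusions differ by arm, the ADR difference can move without any device effect, and the protocol states no analysis that would show it. Separately, sections 7.3.7 and 8.2 treat a subject who meets a criterion differently: withdrawal is optional in one, and removal from the analysis automatic in the other.

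**Working it through.** **Inputs.** Section 8.1 gives a withdrawal allowance of 10%, an enrolment goal of 750 per arm and an interim ADR of 49% under standard colonoscopy (SC). (The Synopsis still carries 400 per arm and 43%; the section 8.1 figures are used here.)

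**The plan's own allowance.** 198 / 0.90 = 220 and 297 / 0.90 = 330, so the inflation step reproduces. The 10% is stated for that goal, not for 750. Carrying it over is an assumption: 750 × 0.10 = 75 excluded and 675 analysed per arm, or 150 of 1,500 randomised subjects outside the analysis.

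**Illustration.** Assume no true effect, ADR 49% in both arms, 10% excluded per arm, and neutral exclusions in SC, which therefore reads 49%. Let f be the share of excluded computer-aided (CC) subjects who have an adenoma. Then

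CC ADR among completers = (0.49 − 0.10 f) / 0.90.

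The last column comes from a simulation with 750 randomised per arm, a one-sided Fisher exact test at 0.025 and 3,000 runs (Monte Carlo standard error near 2.5% is about 0.3 points).

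| f | CC ADR | Shift, points | False superiority |
|---|---|---|---|
| 100% | 0.39 / 0.90 = 43.3% | −5.7 | not simulated; works against the device |
| 49% (neutral) | 0.441 / 0.90 = 49.0% | 0 | 2.6% |
| 40% | 0.45 / 0.90 = 50.0% | +1.0 | 4.4% |
| 30% | 0.46 / 0.90 = 51.1% | +2.1 | 9.9% |
| 20% | 0.47 / 0.90 = 52.2% | +3.2 | 19.7% |
| 0% | 0.49 / 0.90 = 54.4% | +5.4 | 49.6% |

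**Scale.** SE of the difference at 675 per arm = √(2 × 0.49 × 0.51 / 675) = 0.0272. The extremes are therefore about 2 standard errors either way: 0.054 / 0.0272 = 2.0 and −0.057 / 0.0272 = −2.1.

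**A smaller imbalance in number.** If 4% of CC subjects are excluded, all adenoma-negative, against neutral SC exclusions: 0.49 / 0.96 − 0.49 = +2.0 points, z = 0.75 on the same SE.

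**Same mix in both arms.** With f = 20% in each, both read 52.2% and the difference is zero.

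**The case against.** The case for leaving section 8.2 alone has real content.

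- A reader might infer that the superiority claim rests on no randomised comparison at all. The documents do not support that. Subjects are randomised 1:1 and compared by arm, and exclusions unrelated to arm do not bias the null comparison. What is missing is a comparison of everyone as randomised.
- A reader might infer that open-ended discretion decides who is analysed. Section 8.2 refers to the withdrawal criteria, and discretion is not one of the six. On its wording, a completer who meets none of them stays in.
- Not every criterion is an unblinded judgement. Consent withdrawal belongs to the subject, who is blinded. Preparation is graded on a named scale. Stenosis, solid stool and post-surgical anatomy exist before the arm can act, and some criteria mirror the baseline exclusions in section 7.2.2.
- The criteria pull in both directions, so no direction of bias can be presumed.
- Completers match the endpoint as written, and a protocol-compliant set is a recognised analysis for non-inferiority, the hypothesis on which the sample size was stated.
- A statistical analysis plan may add sets or sensitivity analyses, so it cannot be said that none exists.

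These points limit the concern without removing it. The polyposis or inflammatory bowel disease criterion is still judged from the examination by someone who knows the arm, and the superiority test still uses the completer set. Nor is this a detail left to the analysis plan: the protocol fixes both the set and the endpoint denominator, and a plan that analysed all randomised subjects would contradict both.

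**Conclusion.** The point holds in this form: the protocol fixes a single, completer-only population, formed after randomisation partly on unblinded findings, and uses it for both tests. It should be fixed.

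The size of any bias is unknown. The 43.3% to 54.4% range rests on assumptions: 49% true ADR in both arms, 10% excluded per arm, and neutral SC exclusions. A reader might take the upper end, or the roughly 50% false superiority rate that goes with it, as the expected consequence. It is a one-directional extreme; the opposite extreme works against the device, and an equal mix in both arms gives no bias. The defect is that the stated analysis could neither reveal nor rule out such an imbalance.

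**What to change.** - **Sections 8.2 and 7.4.1.** Define the primary set as all randomised subjects, analysed by assigned arm. Score a subject ADR-positive if any histologically confirmed adenoma was removed, whether or not the procedure was complete, and otherwise negative. A subject with poor preparation or suspected polyposis is then scored on what was found. State in advance how non-starters and withdrawn consent are handled; a set limited to subjects who start colonoscopy would not be all-randomised.
- **Section 8.3.** Test superiority in that set. Keep the present completer set as per-protocol and require non-inferiority in both, because scoring incomplete procedures as negative can shrink a difference and so favour non-inferiority.
- **Reporting.** Tabulate exclusions by arm and reason.
- **Sections 7.3.7 and 8.2.** Reconcile optional withdrawal with automatic exclusion. No clinical withdrawal rule need change for the analysis sets to be defined.

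The cost is protocol wording and one extra analysis. Section 7.5 already has outcomes recorded for each enrolled subject. ADR would fall somewhat in both arms. As a bound, if 49% held among completers and a full 10% were scored negative, it would be 0.90 × 49% = 44.1%, and a difference between arms would shrink by the same factor of 0.90.

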## 8.3. Statistical Methods

The primary analysis will be the comparison of ADR between CC and SC. Differences in ADR between two arms will be expressed as relative risk (RR) with 95% CIs.

Non-inferiority will be met for the primary endpoint (ADR) if the lower 2-sided 95% confidence interval (CI) excludes a 10% or greater difference in favor of the control group. The 10% non-inferiority margin reflects a typical maximum clinically acceptable difference for comparative studies.

If non-inferiority is demonstrated for the primary endpoint, the endpoint will be assessed for superiority (one-sided p value <0.025) using the Fisher exact test.

Categorical variables will be described by frequency counts and percentages. Quantitative variables will be described by mean and standard deviations. Chi-square and t-tests will be used to compare categorical and continuous variables between the two groups, respectively.

ADR and PDR will be stratified by subject characteristics (including age, gender, and colonoscopy indication) and experience of the operator; APC and PPC will be stratified by lesion characteristics (including size, location, and morphology of each polyp).

A p value <0.05 will be considered statistically significant.

All statistical analyses will be performed using R or Python software.

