## 8. Statistical Analysis

## 8.1. Sample Size Estimation

The sample size is calculated based on the evaluation of primary outcome ADR. Based on the results of meta-analysis, an expected ADR ranges from around 20% to 40% for AI-aided colonoscopy and SC ([Barua et al., 2021](#); [Hassan et al., 2021](#); [Mohan et al., 2020](#); [Shaukat et al., 2021](#); [Spadaccini et al., 2021](#)). A sample size ranging from 198 to 297 per arm is required to establish non-inferiority with a non-inferiority margin of 10%, power of 80% and an alpha level of 2.5% (one-sided). Considering a withdrawal rate of 10% due to potential exclusions and drop-outs, the enrollment goal is 220 to 330 subjects per arm.

However, interim analysis of this study in March 2023 showed that the ADR in our SC group is 49%, which is significantly higher than the ADR results acquired from meta-analysis (around 20%); therefore, the enrollment goal is increased to 750 subjects per arm. (i.e., 1500 subjects in total. )

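### The ADR non-inferiority margin of 10% has no stated scale: the only interval named is for the relative risk, while the sample size comes from an absolute margin of 10 percentage points

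*Protocol*

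**What the plan says.** Section 8.3 of the protocol sets the effect measure: "Differences in ADR between two arms will be expressed as relative risk (RR) with 95% CIs". This is the only interval for ADR that the protocol names. The next paragraph gives the decision rule: non-inferiority is met "if the lower 2-sided 95% confidence interval (CI) excludes a 10% or greater difference in favor of the control group". The justification adds no scale: "The 10% non-inferiority margin reflects a typical maximum clinically acceptable difference for comparative studies". The synopsis repeats the measure, the rule and the justification.

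Section 8.1 uses a 10% margin, 80% power and one-sided alpha of 2.5%, again without a scale. It assumes that "an expected ADR ranges from around 20% to 40% for AI-aided colonoscopy and SC" and concludes: "A sample size ranging from 198 to 297 per arm is required to establish non-inferiority". It then adds 10% for withdrawals: "Considering a withdrawal rate of 10% due to potential exclusions and drop-outs, the enrollment goal is 220 to 330 subjects per arm". After an interim SC ADR of 49%, the goal was raised to 750 per arm, with no calculation shown.

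**The concern.** A margin needs a scale, and the interval compared with it must be on the same scale. Here the interval is for a ratio, and the margin is called a difference and given as a bare percentage. The outcome is itself a percentage, so 10% can mean 10 percentage points or a relative loss of one tenth (RR 0.90).

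The two readings are far apart. At a control ADR of 49%, one tenth is 4.9 points, about half the absolute margin. At 20% it is 2 points, one fifth of it. This is the success rule for the primary endpoint, so the same data could support or refuse non-inferiority depending on which sentence the analyst follows.

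**Working it through.** **Inputs.** From section 8.1: ADR 20% to 40% in both arms, margin 10%, power 80%, one-sided alpha 2.5%, withdrawal 10%, interim SC ADR 49%, goal 750 per arm. Allocation is 1:1 (section 7.1). Evaluable per arm: 750 × 0.90 = 675. The squared sum of normal quantiles for 80% power is 7.849 at one-sided 2.5% and 6.183 at one-sided 5%.

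**1. The plan's own figure, absolute margin, equal ADRs.** n = (z sum)² × 2p(1−p) / 0.10².

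- At 2.5%: 7.849 × 0.32 / 0.01 gives 252 (ADR 20%); 7.849 × 0.48 / 0.01 gives 377 (ADR 40%). These are not the stated figures.
- At 5%: 6.183 × 0.32 / 0.01 gives 198; 6.183 × 0.48 / 0.01 gives 297. Dividing by 0.90 gives 220 and 330. All four match exactly.

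**2. The same figure, relative margin 0.90, equal ADRs.** n = (z sum)² × 2(1−p)/p / (ln 0.90)², with (ln 0.90)² = 0.01110.

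- At 2.5%: 5,657 (ADR 20%) and 2,122 (ADR 40%).
- At 5%: 4,456 and 1,671.

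The relative reading cannot be the source of 198 to 297. The sizing was absolute.

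**3. Power at 49% in both arms, 675 evaluable, one-sided 2.5%.**

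- Difference: SE = √(2 × 0.49 × 0.51 / 675) = 0.0272. Power = Φ(0.10/0.0272 − 1.96) = 95.7%. For 80% power, 393 evaluable per arm suffice.
- Relative risk: SE of log RR = √(2 × 0.51 / (0.49 × 675)) = 0.0555. Power = Φ(0.1054/0.0555 − 1.96) = 47.5%. For 80% power, 1,472 evaluable per arm are needed, or 1,472 / 0.90 = 1,636 enrolled.

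**4. How far the power figure depends on its assumptions.**

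| Evaluable per arm | True RR | Power, −10 points | Power, RR 0.90 |
|---|---|---|---|
| 675 | 1.00 | 95.7% | 47.5% |
| 750 | 1.00 | 97.2% | 51.6% |
| 675 | 1.05 | 99.6% | 81.1% |
| 675 | 1.10 | about 100% | 96.6% |

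**5. Can the decision differ on the same data?** Wald limits, SC 331/675 (49.0%):

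- CC 304/675 (45.0%): difference −4.0 points, lower limit −0.040 − 1.96 × 0.0271 = −9.3 points, a pass. RR 0.918, lower limit 0.918 × exp(−1.96 × 0.0579) = 0.820, a clear fail.
- CC 331/675 (49.0%): lower limits −5.3 points (pass) and 0.897 (fail, by 0.003).

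**6. Does the scale reach the superiority test?** With SC 331/675, the smallest CC count with one-sided Fisher p below 0.025 is 368. Its RR lower limit is 1.003, far above 0.90, and its difference lower limit is above zero. Any result that shows superiority has already passed non-inferiority on either scale.

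**The case against.** The best defence is that the intended reading can be worked out. The rule speaks of a difference, ADR is defined in section 7.4.1 as a percentage, and the numbers in section 8.1 fit an absolute margin. On this view the relative risk is only how results are reported. Much of this stands: percentage points is the more natural reading, and the fix below adopts it. But the text does not say so, and the only interval it names is on the other scale.

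A reader might infer more than the documents support:

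- *That the plan tests RR above 0.90.* It never mentions 0.90 or a relative margin. That is one possible reading, not the stated rule.
- *That the scale decides access to the superiority test in a way that matters.* Step 6 shows that it cannot change a superiority conclusion.
- *That the trial has under 50% power.* This needs the relative reading, equal true ADRs and 675 evaluable. With all 750 evaluable it is 51.6%. If the 25.2% in section 5 is read as a true RR of 1.252, relative-scale power is close to 100%.
- *That equal observed ADRs would fail on the ratio scale.* This is a knife-edge: with 368/750 in each arm the lower limit is 0.902, a pass. The 45.0% against 49.0% example is the sturdier one.
- *That the scale will be chosen after the data are seen.* The SAP is not shown and may already fix it. The protocol's own pairing would still need correcting.

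**Conclusion.** The point holds as a mismatch within the protocol. The named interval is relative, the margin carries no scale, and the sizing is absolute. The unresolved choice changes the non-inferiority decision over a plausible range of results, where CC is about equal to or worse than SC, and leaves a superiority conclusion untouched.

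Under equal true ADRs of 49% and 675 evaluable, the two readings differ by 95.7% against 47.5% power. The gap narrows quickly if the device is truly better. These figures use normal approximations, the 49% and 750 of section 8.1 (the synopsis still carries 43% and 400), and the 10% withdrawal rate. The power attached to 750 per arm is computed here, not stated in the plan.

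That 198 to 297 matches one-sided 5% rather than the stated 2.5% is a separate error. It does not alter which scale was used.

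**What to change.** In section 8.3 and the synopsis, state that non-inferiority is concluded if the lower limit of the two-sided 95% CI for ADR(CC) minus ADR(SC) is above −10 percentage points. Report the relative risk with its 95% CI as supportive. Add the words 'percentage points' to the margin in section 8.1. The interval method can be left to the SAP, which should be checked for the same scale.

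The cost is a sentence in each place and no additional patients, because the sizing already rests on this scale. If the sponsor did intend a relative margin, it must be stated and justified and the trial re-sized: for RR 0.90 with equal ADRs of 49%, about 1,636 enrolled per arm. Either way, the change should be made before outcome data by arm are analysed.

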### (1) Patient characteristics

- a. Age
- b. Gender
- c. Race
- d. Height
- e. Weight
- f. BMI
- g. Medical history of CRC from any first degree relatives (including parents, siblings, and children)
- h. Smoking

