### (2) Disease-related characteristics

- a. Fecal immunochemical test (FIT) results
- b. Colonoscopy indication

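### Section 8.3 fixes an unadjusted superiority test for ADR and names no covariate for the RR, giving up a small amount of precision that the randomisation factors and baseline data already on the CRF could supply

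*Protocol*

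**What the plan says.** Section 8.3 makes the comparison of ADR between CC and SC the primary analysis: "Differences in ADR between two arms will be expressed as relative risk (RR) with 95% CIs". Non-inferiority requires that the lower limit of the two-sided 95% CI "excludes a 10% or greater difference in favor of the control group". If that is met, superiority is tested by a Fisher exact test at one-sided 0.025. No covariate is named for either step.

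Baseline information enters section 8.3 only as breakdowns: "ADR and PDR will be stratified by subject characteristics (including age, gender, and colonoscopy indication) and experience of the operator". Section 7.3.3 stratifies randomisation by gender, age and indication, but section 8.3 does not say that these factors enter the primary comparison.

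Section 7.5 lists the data to be recorded on the CRF for each enrolled subject. They include "Fecal immunochemical test (FIT) results", CRC in first-degree relatives, smoking, and BMI. None of these four is a randomisation factor, a named breakdown factor or a model term.

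**The concern.** When baseline variables predict whether an adenoma is found, a standardised comparison that uses them has a smaller variance than the raw comparison of two proportions. Leaving the randomisation factors out of the analysis also wastes part of what stratification achieves: the unadjusted standard error does not credit the balance it creates.

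An unseen SAP would be the usual place for covariate detail. Here, however, the protocol has already chosen the superiority test, and a Fisher test on a 2×2 table leaves no room for covariates. An SAP could adjust that test only by departing from section 8.3. At stake is some superiority power in a trial whose enrolment goal has already risen from 220–330 to 750 per arm (section 8.1).

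**Working it through.** **1. The plan's own figure.** Section 8.1 says "A sample size ranging from 198 to 297 per arm is required to establish non-inferiority", with "an expected ADR ranges from around 20% to 40% for AI-aided colonoscopy and SC", a 10% margin, 80% power and one-sided alpha 2.5%. With equal ADRs p and an absolute margin, n per arm = (z₁₋α + z₀.₈)² × 2p(1−p) / 0.10².
- One-sided 2.5%: 7.849 × 0.32 / 0.01 = 251.2, so 252 (p = 20%); 7.849 × 0.48 / 0.01 = 376.7, so 377 (p = 40%).
- One-sided 5%: 6.183 × 0.32 / 0.01 = 197.8, so 198; 6.183 × 0.48 / 0.01 = 296.8, so 297.

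The stated range is reproduced only at one-sided 5%. That is a separate matter. It does not affect what follows, which uses the final enrolment goal.

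**2. Inputs.**
- From section 8.1: 750 per arm, 10% withdrawal, so 750 × 0.90 = 675 evaluable per arm; SC ADR 49%.
- Assumed: a true gain of 7.6 points (49% vs 56.6%), chosen to give about 80% crude power.
- Assumed: an ADR gap between FIT-positive and FIT-negative subjects of 10, 20 or 30 points, with smaller effects for smoking, family history and BMI. The documents give no such values.

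**3. Crude superiority power.** SE = √[(0.49×0.51 + 0.566×0.434)/675] = 0.0271. Power = Φ(0.076/0.0271 − 1.96) = 80.1%. The exact power of the one-sided Fisher test is 79.1%.

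**4. Gain from adjustment.** Results from 4,000 simulated trials per scenario, using an adjusted risk difference with robust SE:

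| FIT gap (assumed) | Crude power | + randomisation factors | + FIT, smoking, family history, BMI | Variance ratio, last two |
|---|---|---|---|---|
| 10 points | 79.5% | 80.1% | 80.6% | 0.991 |
| 20 points | 79.9% | 80.5% | 81.9% | 0.965 |
| 30 points | 79.6% | 80.6% | 83.5% | 0.922 |

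- Gain from the four covariates over the randomisation factors: 0.5, 1.4 and 2.9 points.
- Gain of the full model over the crude analysis: 1.1, 2.0 and 3.9 points.
- Equivalent extra evaluable subjects, 1350 × (1/ratio − 1): 12, 49 and 114.

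The Monte Carlo SE of one power estimate near 80% is √(0.8×0.2/4000) = 0.6 points, so the smallest gain needs a check by formula. Φ(0.076/(0.0271√ratio) − 1.96) gives 80.4%, 81.5% and 83.2% against 80.1%, that is, gains of about 0.4, 1.4 and 3.1 points. The two agree.

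As a second check, assumed odds ratios for the four covariates (FIT 1.3–2.5, family history 1.1–1.6, smoking 1.2–2.0, BMI per SD 1.1–1.35) explain about 1%, 3% and 8% of the ADR variance.

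**5. Non-inferiority with equal ADRs of 49%.** SE = √(2×0.49×0.51/675) = 0.0272; 95% half-width 5.33 points.
- Half-width × (1 − √ratio): the interval narrows by about 0.02, 0.09 or 0.21 points.
- Absolute 10-point margin: Φ(0.10/0.0272 − 1.96) = 95.7% unadjusted. With the ratios above it is 95.8%, 96.3% and 96.9%.
- If the margin were RR 0.90: SE of log RR = √[2×0.51/(0.49×675)] = 0.0555, and power = Φ(0.1054/0.0555 − 1.96) = 47.5%. With the same ratios it is 47.8%, 48.9% and 50.6%.

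**The case against.** The strongest reply is that nothing here is wrong. An unadjusted RR with a Fisher test is a valid analysis, and the choice of covariates normally belongs to the SAP. This largely stands: the point is missed efficiency, not an error. It survives as a comment on the protocol because section 8.3 names a superiority test that rules out adjustment.

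A reader might infer that the RR interval is also fixed as crude. The text does not say so. It names no covariate, but an RR with a 95% CI can come from an adjusted model.

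A reader might also infer that non-inferiority is materially weakened. On an absolute margin it is not, as step 5 shows. Power is low only if the margin is relative. Section 8.3 leaves that scale open, and adjustment would not repair it.

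Further objections also have force:
- Every input that drives the gain is assumed. If the covariates do not predict adenoma, the gain is nil.
- FIT contributes most, but no study procedure performs it. Results may be absent for some subjects and may overlap with indication.
- The SC-arm ADR has been reported at interim looks (43% in the Synopsis, 49% in section 8.1), so changing the primary test now carries some cost in credibility.
- Section 8.2 drops subjects after randomisation. It would therefore be too strong to say that adjustment cannot bias the comparison or that it removes chance imbalance. It reduces the effect of imbalance in the measured covariates, and the unadjusted CI already allows for chance imbalance.

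**Conclusion.** The point holds as an optional, low-cost improvement. Section 8.3 commits superiority to an unadjusted test and leaves both the randomisation factors and four recorded baseline variables out of the stated primary comparison.

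Under the assumed prognostic strengths, the four covariates are worth a 1% to 8% cut in variance beyond the randomisation factors, or about 0.5 to 3 points of superiority power. That rests on 675 evaluable subjects per arm, an SC ADR of 49% and a true gain of 7.6 points. The benefit falls mainly on superiority. The documents do not support reading this as a flaw that threatens the trial's conclusion.

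**What to change.** In section 8.3, prespecify the primary ADR comparison as follows:
- Fit a logistic model with arm, the randomisation factors (gender, age, indication), FIT (positive, negative, not done), family history of CRC, smoking and BMI.
- Standardise over the whole analysis population to obtain one marginal ADR per arm, and report the between-arm effect with its 95% CI. A conditional odds ratio would not serve, because it does not give this gain in precision.
- Use that estimate and interval for both non-inferiority and superiority.
- Keep the crude RR and Fisher exact test as a sensitivity analysis.

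Fix and document the covariates, their coding and the not-done category for FIT before any further arm-level data are seen, and acknowledge the earlier interim looks.

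The cost is a change of wording in section 8.3 and the matching SAP text; no new data are needed. The downside is small: the primary test changes after interim looks at the SC-arm ADR. Adjustment does not cure the post-randomisation exclusions in section 8.2, which need their own treatment.

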### (3) Procedure-related characteristics

- a. Bowel preparation quality (based on the four-grade modified Aronchick Bowel Preparation Scale) ([Hsu et al., 2016](#)): excellent (1), good (2), fair (3), poor (4)
- b. Experience of the operator /endoscopists
- c. Cecal intubation time (min and sec)
- d. Withdrawal time (min and sec)
- e. Effective procedure time (min and sec)
- f. Endoscopy video processor models

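### The superiority test on ADR is an unstratified Fisher exact test although randomisation is stratified by gender, age and indication; it is valid but conservative, at a modest cost in power

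*Protocol*

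**What the plan says.** On allocation, Section 7.3.3 states that "Randomization will be stratified by gender, age, and colonoscopy indication (screening, diagnostic, or surveillance) of subjects", with 1:1 assignment. It gives no cut-points for age and no reason for choosing these factors.

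On analysis, Section 8.3 (repeated in the synopsis) makes superiority on ADR the step after non-inferiority: "the endpoint will be assessed for superiority (one-sided p value <0.025) using the Fisher exact test". The treatment effect is described only as follows: "Differences in ADR between two arms will be expressed as relative risk (RR) with 95% CIs". No stratified or adjusted test or estimate of the arm effect is named.

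The factors reappear once, later in Section 8.3: "ADR and PDR will be stratified by subject characteristics (including age, gender, and colonoscopy indication) and experience of the operator". This reads as a breakdown of rates by subgroup, not as a stratified comparison of the arms.

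**The concern.** Balancing the arms within strata that predict the outcome removes between-stratum variation from the true variance of the difference in ADR. A pooled test still counts that variation as noise, so its standard error is too large and it rejects too rarely. Fisher's test adds a second source of conservatism, the discreteness of the conditional distribution, which serves little purpose at several hundred subjects per arm.

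At stake is power for the superiority claim, which is the improved-ADR half of the study objective. The protocol itself names the test, so this is not a detail left open for the SAP: an SAP that used a stratified test would depart from the protocol.

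**Working it through.** **Inputs from the protocol.** Enrolment goal 750 per arm, SC-arm ADR 49% and withdrawal 10% (Section 8.1; the synopsis still shows the older goal of 400). Evaluable per arm: 750 × 0.90 = 675. One-sided level 0.025 (Section 8.3).

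**Assumptions.** True differences of +5 and +7.5 points (the protocol names no superiority effect), two age bands, hence 2 × 2 × 3 = 12 strata of equal size, and the spread of ADR across strata.

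**The plan's own figure.** The protocol gives no superiority power to reproduce. Its sample size is for non-inferiority: "an expected ADR ranges from around 20% to 40% for AI-aided colonoscopy and SC", with "a non-inferiority margin of 10%, power of 80% and an alpha level of 2.5% (one-sided". Using n = (z_α + z_β)² × 2p(1−p)/0.10²:
- One-sided 0.025: 7.849 × 0.32/0.01 gives 252 at 20%; 7.849 × 0.48/0.01 gives 377 at 40%.
- One-sided 0.05: 6.183 × 0.32/0.01 gives 198; 6.183 × 0.48/0.01 gives 297.

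The stated 198 to 297 therefore matches one-sided 5%, not 2.5%. That is a separate matter, and nothing below depends on it.

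**Step 1: Fisher's discreteness, exact, with no assumption about strata.** Size is the sum over all pairs (x1, x2) of Bin(x1; n, p) × Bin(x2; n, p) where the one-sided Fisher p value is at most 0.025. Power uses the two different rates.

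| n = 675 per arm | Fisher | Uncorrected chi-square |
|---|---|---|
| Size, ADR 20% | 0.0214 | 0.0249 |
| Size, ADR 40% | 0.0216 | 0.0246 |
| Size, ADR 49% | 0.0231 | 0.0252 |
| Power, 49% vs 54% | 43.9% | 45.5% |
| Power, 49% vs 56.5% | 78.0% | 79.4% |

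The loss is about 1.5 points. At 750 per arm, power at +7.5 points is 82.1% against 83.5%.

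**Step 2: ignoring the strata, by hand.** With balance within strata, the ratio of true to pooled variance under the null is 1 − Var(p_s)/[p(1−p)], where p_s are the stratum ADRs and p(1−p) = 0.49 × 0.51 = 0.2499. The size of a pooled normal test is then 1 − Φ(1.96/√ratio). Treating p_s roughly as uniform over its range, Var(p_s) = range²/12:
- 36% to 62%: 0.26²/12 = 0.0056; ratio 0.977; size 0.024.
- 25% to 73%: 0.48²/12 = 0.0192; ratio 0.923; 1.96/0.961 = 2.04; size 0.021.
- 17% to 82%: 0.65²/12 = 0.0352; ratio 0.859; 1.96/0.927 = 2.11; size 0.017.

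**Step 3: both effects together, by simulation.** 200,000 trials per row, 12 strata, 672 per arm (12 × 56), SC ADR 49%. Each cell gives Fisher / pooled chi-square / CMH.

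| Assumed stratum ADR | One-sided size | Power at +5 (%) | Power at +7.5 (%) |
|---|---|---|---|
| all 49% | 0.0228 / 0.0259 / 0.0256 | 43.82 / 45.96 / 45.78 | 77.82 / 79.43 / 79.38 |
| 36% to 62% | 0.0219 / 0.0249 / 0.0249 | 43.58 / 45.78 / 45.78 | 77.83 / 79.44 / 79.45 |
| 25% to 73% | 0.0192 / 0.0221 / 0.0253 | 43.73 / 45.94 / 48.08 | 78.54 / 80.18 / 81.73 |
| 17% to 82% | 0.0159 / 0.0185 / 0.0253 | 43.24 / 45.58 / 50.68 | 79.41 / 81.05 / 84.45 |

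Gain of CMH over Fisher at +5 points: 45.78 − 43.82 = 2.0; 2.2; 4.4; 7.4. At +7.5 points: 1.6; 1.6; 3.2; 5.0. In the widest case at +5, 50.68 − 45.58 = 5.1 comes from stratifying and 45.58 − 43.24 = 2.3 from dropping Fisher. Widening the spread slightly, to about 16% to 83%, takes Fisher's size to about 0.015 and the gain to about 8 points.

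**The case against.** The strongest reply is that nothing here is invalid. Fisher's test is prespecified and keeps its level, and stratifying the allocation while testing unadjusted does not contradict anything in the protocol. The trial is sized for non-inferiority, which is decided by a confidence interval; Fisher enters only afterwards. The protocol states no superiority effect or power. All of this stands and limits the weight of the point. It does not remove the gain: in no scenario tested did Fisher match CMH.

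It also stands that the larger gains rest on assumed stratum ADRs. If the strata predict ADR only weakly, almost all the gain comes from dropping Fisher, and an uncorrected chi-square would recover it.

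A reader might be tempted to infer more, which the documents do not support:
- **That the superiority result would be unsound or the trial underpowered.** The error is in the safe direction, and no promised power is shown to be missed.
- **That the factors were chosen because they predict adenomas.** This is plausible, but Section 7.3.3 gives no reason.
- **That the primary analysis must also adjust for site and operator.** Section 7.5 lists "Experience of the operator /endoscopists", and operator experience is used in the ADR breakdown. Site is not itemised there, and neither is a randomisation factor.
- **That the Fisher p value and the RR interval will conflict.** The interval method is not named. Assuming a Wald interval on log RR, disagreement occurs in about 0.4% to 0.6% of trials at 675 per arm, and about 1% at 750.

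**Conclusion.** The point holds as one of efficiency and coherence, not validity. The protocol fixes a superiority test that does not use the factors it randomises by and that is conservative in its own right. Fisher's exact one-sided size at 49% ADR and 675 per arm is about 0.023, whatever the strata do. It drops to between about 0.022 and 0.015 if stratum ADRs range from 36–62% to about 16–83%, while CMH stays at about 0.025.

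The power given up is about 1.5 to 2 points from Fisher alone and about 2 to 8 points in total. The upper end needs strongly prognostic strata and a true difference near 5 points. These figures assume 10% withdrawal from 750 per arm, two age bands and equal stratum sizes. The change is worth making because it needs no additional subjects, but it is a modest improvement.

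**What to change.** In Section 8.3 and the synopsis, make the superiority test a Cochran-Mantel-Haenszel test at one-sided 0.025, stratified by gender, age group and indication as randomised. State the age bands used in the randomisation list. Report the matching stratified effect estimate with its 95% CI, on the scale used for the non-inferiority decision, so that estimate and test belong together. Keep Fisher's exact test as a sensitivity analysis.

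The cost is small: age, gender and indication are already collected under Section 7.5. But the synopsis and Section 8.1 report interim looks at the SC-arm ADR (October 2022 and March 2023). Replacing a prespecified test with a more powerful one after such looks calls for a dated amendment that gives the reason and records that it was made without sight of between-arm results.
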